## Abstract

**Background:**

Prolonged sitting, a significant risk factor for increased morbidity and mortality, is accumulated mostly in the workplace. There is limited research targeting specific at-risk populations to reduce occupational sedentary behaviour. A recent study found that professional males have the longest workplace sitting times. Current evidence supports the use of multi-level interventions developed using participative approaches. This study’s primary aims are to test the viability of a future definitive intervention trial using a randomised pilot study, with secondary aims to explore the acceptability and feasibility of a multicomponent intervention to reduce workplace sitting.

**Methods:**

Two professional companies in Dublin, Ireland, will take part in a cluster randomised crossover pilot study. Office-based males will be recruited and randomised to the control or the intervention arms. The components of the intervention target multiple levels of influence including individual determinants (via mHealth technology to support behaviour change techniques), the physical work environment (via provision of an under-desk pedal machine), and the organisational structures and culture (via management consultation and recruitment to the study). The outcomes measured are recruitment and retention, minutes spent sedentary, and physical activity behaviours, work engagement, and acceptability and feasibility of the workplace intervention.

**Discussion:**

This study will establish the acceptability and feasibility of a workplace intervention which aims to reduce workplace SB and increase PA. It will identify key methodological and implementation issues that need to be addressed prior to assessing the effectiveness of this intervention in a definitive cluster randomised controlled trial.

**Supplementary Information:**

The online version contains supplementary material available at 10.1186/s40814-020-00716-9.

## Introduction

### Background and rationale

Prolonged periods of daily sedentary behaviour (SB) are associated with increased mortality, cardiovascular morbidity, diabetes [1–3], some cancers [4, 5], depression [6], and decreased self-rated health [7]. SB has been defined as any waking behaviour while in a sitting or lying position that expends ≤ 1.5 metabolic equivalents (METs) of energy expenditure (EE) [8]. Being sedentary for more than 7 h per day is associated with increased all-cause and cardiovascular mortality rates [3, 9]. Although high levels of physical activity (PA) may attenuate these relationships, 60–75 min per day of moderate physical activity (MPA), or 3.5 times the World Health Organization’s (WHO) PA recommendations of 150 min of MPA per week, are required to eliminate the detrimental effects of SB [9]. Time spent in SB has increased rapidly in middle- to high-income countries in recent years and is set to continue to do so without intervention [10]. Given the detrimental health impact of prolonged and uninterrupted daily SB, this presents a serious public health concern.

The settings approach moves interventions upstream from defining goals and targets in terms of populations or individuals only, towards identifying goals that focus on changes in organisations, systems, and the environment [11, 12]. In this context, all of the opportunities for influencing health within a setting can be considered priorities for change, which can lead to maximised health gain [13]. The WHO includes the implementation of multicomponent interventions in a workplace setting to target physical inactivity as one of their ‘best buy’ recommendations for the prevention and control of non-communicable diseases [14].

Working adults spend more than 7.5 h of their day being sedentary, and when individual, social, and environmental factors are controlled for, professional males with high levels of education and who live in an urban location have the longest sitting times [15–17]. High levels of occupational SB are associated with depression and anxiety [18], increased BMI [19], and risk of heart failure [20], mortality in men [21], colorectal cancer [22], pancreatic cancer [23], lung cancer in women [23], and breast cancer in women aged younger than 55 years [24]. Reducing workplace SB is important to curtail the physical and mental health risks associated with prolonged SB [6, 25–27]. Individuals in private offices sit more and engage in more prolonged sitting than those in public office spaces suggesting that this group may be at increased risk of the associated health outcomes [28].

Given the strong reinforcing and restrictive properties of the physical and social environment of the office workplace, allowing workers to continue with their favoured or required task (e.g. computer work), while breaking up prolonged SB may be most acceptable and effective in terms of workplace interventions to address SB [29]. Studies examining sit-stand workstations have enabled the break-up of prolonged SB by replacing some SB with standing; however, standing does not provide the metabolic benefits of light physical activity (LPA) [30]. A recent study employing a data compositional approach showed that standing (and SB) was associated with increased body mass index (BMI), body fat, and fat mass [31]. Standing for long periods may indeed be detrimental to cardiovascular health and has been associated with an increase in the risk of ischemic heart disease and varicose veins [32]. Rempel and Krause [33] suggest that advising sedentary employees to increase standing time at work should not be recommended, and maintain that if the basis for a reduction in SB is to improve cardiovascular health, promotion of increased standing is misguided. Results from studies using treadmill desks [34] and activity-permissive workstations [35] suggest that combining simultaneous, low-intensity PA with sedentary practices could increase daily caloric expenditure and reduce cardio-metabolic risk factors. ‘Active sitting’ as opposed to ‘reduced sitting’ may be preferred in workplace interventions where the choice of employees and/or employers may be to remain seated [36]. Furthermore, combining PA with sedentary activities could reduce time-related costs of PA—a frequently cited barrier to regular PA in adults [37].

Ensuring relevance and individualisation are effective basic methods in health interventions, and this is traced especially to social cognitive theory (SCT) [50]. The core determinants of health behaviour in SCT are knowledge of health risks, perceived self-efficacy, outcome expectations, health goals, perceived facilitators and barriers, and social and structural impediments to change. In a recent review of behaviour change techniques (BCTs) used in SB reduction interventions among adults, the most frequently used intervention functions were enablement (i.e. facilitating reduction in SB), education, and environmental restructuring. The most commonly used (and also most promising) techniques were setting behavioural goals, providing unspecified forms of social support, and addition of objects to the environment [51].

Contemporary technological advances in digital tools such as mobile phones, the Internet, and wearable technology provide a platform to intervene on an individual level to change behaviours. A systematic review and meta-analysis of interventions using computer, mobile, and wearable technology to reduce SB reported a mean reduction of 41 min per day in interventions that used these tools. The most frequently used BCTs were prompts/cues, self-monitoring of behaviour, unspecified social support, and goal-setting [52].

Mobile health (mHealth) technology has rapidly gained popularity in the general population. mHealth technology includes wearable PA monitors and trackers that connect to smartphone applications (apps). These apps allow individuals to manage their own health and wellbeing at a relatively low cost and offer potential to tailor interventions to the needs of individuals or specific groups. A recent review to investigate the use of mHealth in interventions found reasonable evidence that mHealth may be an effective and feasible method to increase PA, with some evidence for effectiveness in reducing SB [53]. Studies using mHealth to promote PA and reduce SB in the workplace found significant reductions in sedentary time in women [54], where the outcomes were increasing daily steps [55, 56], or reductions in computer use as a proxy for SB [57]. Team-based competition as opposed to individual monitoring has been found to increase compliance with wearing activity monitors [53].

Adopting a participatory approach to intervention development and evaluation of an intervention’s acceptability and feasibility benefits the development of effective interventions [58, 59]. Pretesting the participants’ knowledge, beliefs, and circumstances and using this information as a basis for intervention development creates relevance [60]. For interventions to be acceptable, feasible, and effective, participant involvement provides important information on the individual, organisational, and cultural contexts into which SB reduction strategies must be embedded.

### The present study

This study operationalises the Eldridge et al. [61] definition of a randomised pilot study, i.e. those studies in which the future RCT, or parts of it, including the randomisation of participants is conducted on a smaller scale. Feasibility outcomes which ‘might be interviews to ascertain the acceptability of an intervention’ are also investigated within Eldridge et al.’s feasibility study description [61].

Previous research attests to the potential efficacy of combining pedal machines and motivational behaviour change strategies. However, to our knowledge, no studies have combined BCTs of goal-setting, social comparison, self-monitoring, and prompt/cues in a multicomponent intervention using mHealth technology, an ergonomic under-desk portable pedal machine, as well as targeting organisational support by recruiting management staff to participate, in a male-only sample. Pilot work can aid in the design of future trials with continuous outcomes by providing estimates of population SD, evidence of potential for intervention effectiveness, and quantification of feasibility in the form of recruitment and retention rates [62]. This paper outlines the protocol for a randomised pilot study which will employ a cluster randomised controlled wait-list crossover design.

#### Aims and objectives

The study aims to:
To conduct a randomised pilot study to test a set of feasibility objectives to ascertain if a future RCT is viableTo investigate the acceptability and feasibility of a multicomponent intervention to reduce SB by promoting active sitting and LPA in professional male office workers

The objectives of this study will test the feasibility and viability of the intervention in a future larger trial by reporting recruitment and retention rates, and potential intervention effectiveness by ascertaining if participants in the intervention period differ in occupational and overall SB and PA (including cycling time) compared to the control period. This will be addressed by collecting accelerometry data, which will provide information on minutes spent sedentary, standing and moving. The objectives also include an investigation of the acceptability of the intervention using semi-structured interviews and focus group data which will explore participants’ views of acceptability and usefulness and their expectations and experiences of the study. The study will measure intervention acceptability, appropriateness, and feasibility using a questionnaire administered to participants immediately post-intervention [63].

## Methods

### Design

#### Intervention development process

This intervention was developed using guidance from the Medical Research Council (MRC) [64, 65] and encompasses three distinct phases. The first preclinical stage was a literature review of workplace interventions to reduce SB and the application of socio-ecological theory to the design of the current intervention.

Phase I involved the identification of intervention components and the underlying mechanisms by which the outcomes will be influenced. The development of the intervention followed the principles of the integrated approach of socio-ecological theory: a method that emphasises the need to consider multiple levels of influence on behaviour. Qualitative testing and the adoption of a participatory approach through focus groups and semi-structured interviews with both employees and managers have been conducted to help understand the relevance of the intervention components as well as potential barriers to behaviour change.

This protocol outlines phase II of the approach that tests the acceptability and feasibility of an intervention to reduce workplace SB to develop an optimum intervention, as well as feasibility objectives to test the viability of a future trial. The dominance of progression criteria has been noted as relatively crude and somewhat binary assessments of acceptability and feasibility (e.g. [53]). Assessing the acceptability and feasibility of complex interventions in terms of what works, for whom and under what circumstances, and aiming to refine hypotheses about potential mechanisms of action and how these might vary by context has been suggested as more appropriate to better develop interventions [66] and can be integrated to the MRC framework [65, 67]. By exploring the views of those involved by collecting rich qualitative data, as well as contextual exploration, enables optimisation of intervention design or how to adapt to different contexts prior to a full RCT. Piloting the processes of a full RCT such as randomisation and assessing qualitative data provides insight without biasing outcome measurement, e.g. Hawthorne effect, and can assist in hypothesis refinement.

The intervention comprises the provision of the following components: (1) an under-desk portable pedal machine (DeskCycle2; 3D Innovations LLC., Greeley, CO, USA), (2) Garmin Forerunner 35 activity tracker, and (3) access to a Garmin Connect application (app) and website (Garmin.com). The organisational-level component will be targeted by recruiting management staff to the study, thereby garnering support for employees to participate in the pilot study.

The intervention will communicate the key message: ‘cycle at work’. As highlighted from prior qualitative work, the determinants goal-setting, self-monitoring, and social comparison will be included using BCTs provided within the Garmin Connect app/website. Gender-sensitised interventions that recognise men’s interests and tailor health promotion efforts for this specific group have been found to be more effective in increasing physical activity [68, 69]. Social comparison will be used as a strategy to focus on the masculine ideal. By engaging men in PA, this draws upon as well as provides opportunities to garner masculine capital by affirming competitiveness and/or striving for physical prowess [68, 70]. Social comparison will be targeted by providing weekly feedback of each team’s progress. Participants will also be prompted to move every 60 min of accumulated SB using the ‘move’ prompt on the Garmin Forerunner 35 wrist-worn device.

Figure 1 shows an overview of the study timeline. The intervention and control arms will be conducted over 14 days each. The active intervention will involve the use of an under-desk pedal machine to interrupt SB every hour and accumulate ≥ 30 min of cycling time during the working day. There will be a washout period of 1 week between the intervention and control arms. The washout period is used as there is a possibility that the effect of a treatment/intervention in one period may carry over into the next period [71]. These are known as carryover effects. Unless both carryover and period effects are known to be negligible, a crossover design loses its advantages. In order to ensure negligible carryover effects, there is a need to have sufficient washout periods between intervention periods. In circumstances where a participant suffers any adverse outcome such as pain or discomfort while taking part in the study, they will be advised to immediately discontinue participation in the study and to contact their doctor.

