Contextual SB information will be measured using self-report via Ecological Momentary Assessment (EMA). The use of EMA has been recommended to collect ecologically valid and context-specific outcome data alongside objective measures in studies [77, 78]. EMA involves repeated sampling of participants’ current behaviours and experiences in real time and in their natural environments. This is useful to specify the type of activity or contextual factors (e.g., physical, social, temporal, affective) surrounding these behaviours which are important factors to consider when developing interventions and that cannot be provided by objective measures [79]. EMA has been reported as a valid and reliable measure of SB and PA in adults [80] and for use in a workplace setting [81]. Each day, six notifications will appear on participants’ own mobile smartphones at random times between 8 am and 10 pm, using the application PIEL Survey (pielsurvey.org, v1.2.4.2). The notifications are scheduled at random times to obtain a representative sample of participants’ activities over the course of their study participation. The questions have been found to be valid and feasible [82].

Work engagement will be measured at baseline, post-control arm, and post-intervention arm using the Utrecht Work Engagement Scale (UWES-9) [83]. The perceived benefits of reducing SB in the workplace will also be assessed at these time points using a questionnaire devised by the research team. Immediately upon finishing the study, participants will be asked to complete a questionnaire to assess the acceptability, appropriateness, and feasibility of the intervention [63].

Focus groups and semi-structured interviews will be carried out within the 2-week post-intervention follow-up. An interview schedule has been designed based on existing literature. The interview schedule for the focus groups will be guided by Orsmond et al. [84]. The schedule will be pre-piloted on a small number of employees within the author’s place of work, within the Discipline of Public Health and Primary Care.

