#### Feasibility outcomes

The following quantitative measures will be used [63]:
Intervention appropriateness measure (IAM)Acceptability of the intervention measure (AIM)Feasibility of the intervention measure (FIM)

Evaluation of participants’ perspectives of the intervention will be assessed via focus groups and/or semi-structured interviews using the following themes:
Experience of using the under-desk pedal machines, including factors perceived as affecting the pedal machine, issues (e.g. contextual, practical, individual, or others), and adverse consequences (e.g. work, health, or otherwise related)Experiences of the mHealth intervention components (e.g. Garmin watch)Organisational-level and management perspectives on using the pedal machineAcceptability of the overall intervention by the users, from a management and employee perspective

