##### Protocol adherence criterion

Green—≥ 80% of participants engage in > 60% of their cycling goal

Amber—60–79% of participants engage in > 60% of their cycling goal

Red—<60% of participants engage in > 60% of their cycling goal

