##### Retention progression criterion

Green—≥ 80% of participants provide main trial-related outcomes (SB/PA) at T2

Amber—60–79% of participants provide main trial-related outcomes at T2

Red—< 60% of participants provide main trial-related outcomes at T2

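### Men with pain or discomfort are advised to leave the study rather than stop pedalling, so those least able to tolerate the machine are likely to be missing from the acceptability evidence

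*Protocol article*

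**What the plan says.** The rule is in the protocol article under Intervention development process. Its trigger is any adverse outcome during study participation, with pain and discomfort as the examples. The instruction for those affected is that "they will be advised to immediately discontinue participation in the study and to contact their doctor". No severity or relatedness threshold is given, and stopping the pedal machine while staying under assessment is not offered.

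The evidence for the second aim, acceptability and feasibility, is collected later:

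- Aims and objectives places the acceptability, appropriateness and feasibility measures (AIM, IAM, FIM) after the intervention, "using a questionnaire administered to participants immediately post-intervention".
- Assessments says: "Immediately upon finishing the study, participants will be asked to complete a questionnaire to assess the acceptability, appropriateness, and feasibility of the intervention".
- Assessments also says: "Focus groups and semi-structured interviews will be carried out within the 2-week post-intervention follow-up". Feasibility outcomes makes adverse consequences of the pedal machine a theme of these sessions.

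The period comparison is set out under Aims and objectives as "ascertaining if participants in the intervention period differ in occupational and overall SB and PA (including cycling time) compared to the control period". Under Randomisation, each worksite starts with either the intervention or the control period. The only handling of leavers that the article states, under Recruitment and retention, is that dropouts are counted.

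**The concern.** Two separate decisions have been joined: stopping a device that hurts, and leaving the study. The first is a safety matter. The second has no safety purpose where the remaining assessments are harmless to the participant.

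Men who could not tolerate the machine are among the most informative for aim 2. If they follow the advice during the intervention, they leave before the questionnaire and before the interviews. Those who remain are then selected for tolerance, so acceptability tends to be overstated and adverse consequences under-described.

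The crossover adds a second loss, which depends on sequence. A man at the intervention-first site who leaves during the intervention has no control period at all, while a man at the control-first site has already completed his. Sequence is allocated by worksite, so this loss falls on one company only.

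**Working it through.** The plan gives no figure to reproduce: the sample size is pragmatic and no stopping rate is stated. The check is therefore a day count from the protocol, followed by illustrations on stated assumptions.

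**Inputs from the protocol article.** Baseline activPAL wear 9 days, and 14 days in each of the control and intervention periods (Assessments); 30 men (Sample size). Planned activPAL days per man: 9 + 14 + 14 = 37.

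**Days lost per stopper.** Let a man leave after intervention day *d*, with *d* from 1 to 13.

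| | Intervention-first | Control-first |
|---|---|---|
| Intervention days lost, 14 − *d* | 13 to 1 | 13 to 1 |
| Control days lost | 14 of 14 | 0 of 14 |
| Total lost of 37 | (14 − *d*) + 14 = 27 to 15 | 14 − *d* = 13 to 1 |
| Share lost | 73% to 41% | 35% to 3% |

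These counts need no assumption beyond the man following the advice during the intervention.

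**Men with both periods at the intervention-first site (illustrative).** Assume 15 men there, range 10 to 20.

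- One stopper: 14/15 = 93% (9/10 = 90% to 19/20 = 95%).
- Three stoppers: 12/15 = 80% (7/10 = 70% to 17/20 = 85%).

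**Representation in the aim 2 evidence (illustrative).** If a share *s* of men would stop and a fraction *f* of them still respond, stoppers make up *s·f* / (1 − *s* + *s·f*) of respondents. With *s* = 20%:

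- *f* = 1: 0.20/1.00 = 20%, the true share.
- *f* = 0.5: 0.10/0.90 = 11%.
- *f* = 0: 0%.

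With *f* = 0.5, a true 10% appears as 0.05/0.95 = 5.3%, and a true 30% as 0.15/0.85 = 17.6%.

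**Shift in a mean acceptability score (illustrative).** Assume stoppers would score 0.5 to 2.0 points lower and none respond. With *k* stoppers among 30, the observed mean is too high by gap × *k*/30:

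- *k* = 1: 0.02 to 0.07.
- *k* = 3: 0.05 to 0.20.
- *k* = 6: 0.10 to 0.40.

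**Effect on the progression criteria.** Adherence counts men who exceed 60% "of their cycling goal". Assume 10 working days in the period, a cumulative goal, and the goal exactly met until stopping. A man who stops after working day 6 reaches 6/10 = 60%, which is not above 60%, so he counts against adherence. One who stops after working day 7 reaches 70% and can still count as adherent. Retention is judged on the share "of participants provide main trial-related outcomes (SB/PA) at T2", so a stopper also counts against retention if his T2 data are missing. Both effects mostly work against progression.

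**The case against.** The strongest reply is that the bias is inferred. Nothing excludes a man who stops from the questionnaire or an interview, and a questionnaire given on finishing the study could be read as covering someone who finishes early. The plan plainly wants evidence on adverse consequences. How leavers are followed up is the kind of detail a full protocol or information leaflet would hold, and a condensed article need not repeat it. That last point would answer a complaint of omission, but the finding rests on the instruction itself, which directs men out of the study. No other text in the article keeps them in. That leavers are not barred does stand, and it is why under-representation is called likely rather than certain.

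A second reply is that little depends on it. The quantitative analysis is descriptive, no paired analysis is specified, and nine baseline days exist for every man. AIM, IAM and FIM are not progression criteria. Health screening, light-intensity pedalling and a 14-day exposure all suggest few stoppers. These points stand and limit the size. The baseline days do not replace the control period, however, because the stated comparison is between the intervention and control periods.

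A third reply is that the illustrative figures rest on assumed stopper numbers, score gaps and site sizes. That is correct. Only the per-stopper day counts come from the document.

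**Conclusion.** The point holds as a worthwhile, low-cost improvement. The advice sends a man with pain or discomfort out of the study when it need only take him off the machine. Those who follow it during the intervention are likely to be under-represented in the acceptability and adverse-consequence evidence, and at the intervention-first site they lose the whole control period.

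The firm part of the size is per stopper: 14 of 14 control days lost if intervention-first against none if control-first. The overall size is unknown because no stopping rate is given. It is negligible with one stopper and becomes noticeable at around three to six of 30, on the assumptions stated. It does not threaten the go/no-go rule. Stoppers mostly count against adherence and retention, although the reason for a poor result could then be obscured, with intolerance appearing as dropout.

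**What to change.** Reword the sentence so that affected participants are told to *discontinue use of the pedal machine (or the device causing discomfort) and contact their doctor*. Then add that:

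- willing participants are invited to continue the scheduled activPAL, EMA and questionnaire assessments, subject to medical advice, including a control period if one follows;
- AIM, IAM, FIM and an interview are offered at or soon after stopping;
- UWES-9 stays at its scheduled time points.

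The reference to other devices matters because the rule as written also covers discomfort from the thigh monitor or its dressing.

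The cost is one sentence in the protocol and the information leaflet, and an existing questionnaire and interview offered earlier. The downside is a small extra burden on men who stop and agree to continue. The safety advice is preserved, and participants remain free to withdraw altogether.
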